#### Blood collection

Folate (Serum and RBC) levels will be assessed, at baseline (prior to supplementation), every 12 months after enrollment, and at pregnancy. B12 levels will be assessed at baseline and subsequently every year to monitor for B12 deficiency. Folate and B12 tests may be conducted at the own laboratory facilities of the clinic/hospital when available or alternatively at local laboratories determined by the Co-Principal Investigator. The Clinical Coordinator and Co- Principal Investigator will monitor B12 levels and will refer subjects with B12 deficiency to the hematology service for treatment. Randomized subjects found to be B12 deficient may be temporarily or permanently suspended from the study drug based upon recommendations of the hematology referral.

Based on clinical and research experience, few subjects (perhaps none) are expected to ask for their blood results. If requested prior to the end of the study, an independent physician serving in the clinic will provide confidential results to the subject. The subject will also have the opportunity to discuss what her results mean (in terms of being within normal range or not) with the physician independently from other study subjects and research unit staff. This procedure will prevent sharing the results with other study participants as well as with any member of the research team. Since no data is available on what these folate measurements will actually mean in terms of the levels of folic acid supplementation that are provided, it would be impossible for any single woman to interpret these data points in a way that could result in her un-blinding. Therefore, any disclosure of folate test results under these specific circumstances will not affect the blinding of study subjects or of research unit personnel.

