#### Secondary hypotheses

The following secondary hypotheses will be evaluated:

An increase in serum and/or red cell folate levels in all women following daily supplementation with folic acid.

When compared to the 0.4 mg supplemented groups, the 4 mg per day group will have the following:

‐Greater increases in serum and/or red cell folate.

‐Decreases in the recurrence of NSCL/P in each of the following subgroups:

•Women with NSCL/P themselves

•Women with one or more children with NSCL/P

‐A decrease in the severity of NSCL/P in offspring of trial mothers.

‐No increase in twinning rates.

No increase in miscarriage rates.

No increase in rates of preeclampsia.

‐No increase in rates of other birth defects.

‐No decrease in birth weight

‐No decrease in gestational age

A decrease in recurrence of NSCL/P in the group of study subjects compared to an historical control group obtained from the populations served by the craniofacial clinics participating in the study.

A greater decrease in the recurrence of NSCL/P in the group of study subjects receiving 4 mg of folic acid when compared to the historical control group relative to that of the group receiving 0.4 mg when compared to the same control group.

Under separate funding we will examine the role of genes involved in folate metabolism on folate, B12 and homocysteine levels, as well as potential interaction between these genes and the supplementation dose. This project will also establish a resource to examine the long-term outcomes of infants exposed to high dose folic acid in utero.

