#### Randomization procedures

Study subjects will be randomized to either 4mg or 0.4mg of folic acid. The study will be double-blinded; subjects, investigators and research staff will be blinded to the randomization assignments.

The Data Center will prepare the randomization sequence for the study using permuted blocks of random size. Randomization occurs at the subject level and is stratified by study site to ensure a balanced site representation in both treatment groups. The randomization will not be stratified according to risk group (mother with oral cleft or mother of child with oral cleft) or other factors due to the large sample size. As shown in
[121], stratification becomes irrelevant after the sample rises above 200 subjects. Since randomization occurs at the mother’s level, the sample allocation should be very well balanced with respect to the risk group and other factors.

The randomization sequence will link the treatment assignment (0.4mg or 4mg) to a sequential list of serial numbers to be used for the study pill boxes. The Data Center will generate the randomization sequence. The Data Center will supervise the labeling of the boxes with the serial number. In addition, the boxes will be numbered in order of dispensing (1, 2, 3, etc.3). The serial and dispensing order numbers will be recorded on the study visit/follow-up form to track dispensing.

The random assignment will be accomplished by assigning the next serial number in the randomization list as the enrollment of each new subject is confirmed. Once confirmed, the study subject ID is recorded in a computerized randomization log (that will include randomization order, serial number of assigned pill box and the study subject ID). The Clinical Coordinators will affix the study subject ID labels to the boxes of each subject with the serial number assigned to her.

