FA09&10	Miscarriage/Stillbirth Form (With Doctor)	Documents the miscarriage or stillbirth date and age, as well assessment of miscarriage/still birth product if available including the presence or absence of clefting and other malformations, etc.	Co-Principal Investigator, Clinical Coordinator
FA11	Delivery Form (With Subject)	Documents date of delivery, birth weight and sex of the infant, mother’s smoking and drinking habits while pregnant, and any complications and malformations associated with the baby.	Clinical Coordinator
FA12	Delivery Form (With Doctor)	Documents any malformations that may be associated with the baby including craniofacial malformations and abnormal delivery events. Filled with the subject’s doctor (if possible) or abstraction from the medical records of the subject.	Clinical Coordinator
FA13	Phone Call Form	Documents telephone calls made to the study office by the study subjects, the reason for each call, and the action taken.	(Clinical Coordinator, Co-Principal Investigator)
FA14	Study Termination Form	Documents withdrawal from the study by a study subject, the reason(s) for termination and approval (or not) for a two-month post termination follow-up.	Clinical Coordinator
FA15	Post Termination Follow-up Form	Confirms address information, documents menstruation and whether or not the former study subject has gotten pregnant.	Clinical Coordinator
FA16	Laboratory Form	Documents the date of blood collection, date of analysis, and results of the blood testing.	Clinical Coordinator
FA17	Adverse Events Form	Documents all information related to any adverse event encountered during the course of the study.	Clinical Coordinator/Co-Principal Investigator
FA18	Protocol Violations Form	Documents all information related to any protocol violation encountered during the course of the study.	Clinical Coordinator/Co-Principal Investigator
FA19	Pregnancy Confirmation Form	Documents the results of a performed pregnancy test after randomization and related schedule of study folic acid supplementation	Clinical Coordinator
FA20	Prenatal Form (With Subject)	Documents via periodic contacts with the subject, information about pregnancy progress, prenatal vitamins, illness, ultrasound results, smoking/alcohol etc.	Clinical Coordinator

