FA21 and FA21 Suppl-ement	Delivery Form (In-Person Evaluation of Live Birth	Documents the presence or absence of malformations and/or complications with birth upon in-person evaluation of the live born by the Clinical Coordinator.	Clinical Coordinator or Co-Principal Investigator and clinical geneticist (or pediatrician)
FA22 (Outreach-model only)	Pre-Contact Form	Documents the outcome of each attempt to contact subject by the study staff or voluntary professionals assisting on the study.	A study team member, Social worker, Parent Coordinator

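### Routine laboratory form handling gives the staff who assess infants access to post-baseline folate, a marker of dose, and the blinding safeguard does not cover this route

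*Protocol article*

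**What the plan says.** All references are to the protocol article.

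- **Blinding.** Randomization procedures states: "The study will be double-blinded; subjects, investigators and research staff will be blinded to the randomization assignments".
- **Folate sampling.** Blood collection states: "Folate (Serum and RBC) levels will be assessed, at baseline (prior to supplementation), every 12 months after enrollment, and at pregnancy".
- **Expected effect of dose on folate.** Secondary hypotheses lists, for the 4 mg group against the 0.4 mg group: "Greater increases in serum and/or red cell folate".
- **Who records folate.** Table 2 describes FA16, completed by the Clinical Coordinator, as the form that "Documents the date of blood collection, date of analysis, and results of the blood testing". Tables 4 and 5 list FA16 for the yearly sample and for the folate level at pregnancy.
- **Other access.** The job descriptions have coordinators check laboratory data, mainly for B12, and have the Co-Principal Investigator oversee the blood analysis. Routine reports for local use may include laboratory results.
- **Who assesses outcomes.** Table 2 describes FA21 as the form that "Documents the presence or absence of malformations and/or complications with birth upon in-person evaluation of the live born by the Clinical Coordinator". Follow-up of study subjects assigns the in-person infant examination to the Clinical Coordinator or Co-Principal Investigator and names both among those who may review gestational losses.
- **The safeguard.** A woman who asks for her results receives them from an independent physician. Of that arrangement Blood collection says: "This procedure will prevent sharing the results with other study participants as well as with any member of the research team". It adds that "it would be impossible for any single woman to interpret these data points in a way that could result in her un-blinding". It then concludes that disclosure in those circumstances leaves the blinding of subjects and research personnel intact.

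**The concern.** The safeguard guards a rare event: the protocol itself expects few requests from women, perhaps none. The routine route, in which the coordinator enters each post-baseline folate value on FA16, is not addressed. If the folate hypothesis is true, those values carry information about arm, and the people who see them also decide how outcomes are recorded.

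Double-blinding is one of the main advances the protocol claims over earlier cleft recurrence studies. A coordinator who suspects the arm could, without intending to, vary adherence coaching, effort to trace a woman after delivery, how closely an infant is examined for minor defects, the severity score, or the judgement that a cleft is non-syndromic.

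**Working it through.** The protocol gives no figure to reproduce on this point, so the check is mainly a side-by-side reading.

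**1. Does an on-treatment value reach the site before the outcome is assessed?** Samples fall every 12 months and at pregnancy. Table 5 ties the pregnancy sample chiefly to pregnancies in the first year of supplementation; later ones follow a yearly sample. If the schedule is kept, a woman who gives birth will normally have at least one on-treatment folate value on FA16 before her infant is examined. Baseline folate is also collected, so the change can be seen.

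**2. Do the same roles see folate and assess outcomes?**

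| Task | Clinical Coordinator | Co-Principal Investigator |
|---|---|---|
| Folate results | Completes FA16; checks laboratory data | Oversees laboratory analysis |
| Pill compliance and follow-up | Completes FA05 | – |
| Infant examination | Yes (FA21) | Yes (FA21) |
| Review of gestational loss | Yes (FA09&10) | Yes (FA09&10) |

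Nothing in the article withholds post-baseline folate from either role, or requires an infant examiner without access to it.

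**3. Is folate informative about arm?** The dose ratio is 4 / 0.4 = 10, and the trial hypothesises a greater folate rise on the higher dose. Blood collection argues that no data link folate measurements to the supplementation level. That sits badly with the hypothesis. The pilot section also reports that post-supplementation folate was already being measured at the clinic sites. Moreover, a coordinator sees many women's values, so the argument about one woman reading her own does not carry over.

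**4. How informative?** The document gives no folate means or standard deviations by arm, so only an assumed range can be shown. With normal values, equal variances, 1:1 allocation and a between-arm separation of d standard deviations, the best guess from one value is right with probability Φ(d/2):

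| Assumed d | Probability of guessing the arm correctly |
|---|---|
| 0 | 0.50 |
| 0.5 | 0.60 |
| 1 | 0.69 |
| 2 | 0.84 |
| 3 | 0.93 |

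Any true separation lifts the guess above chance. Baseline and repeat values could add to it; variable adherence, other vitamin use and flour fortification would blur it.

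**The case against.** **The safeguard text is narrower than it first looks.** A reader might infer that the protocol promises to keep all folate results from the research team and then breaks that promise. It does not. The sentence on not sharing results, and the one on personnel blinding, both concern release to a woman who asks. The defect is an unaddressed route. This objection stands, and the point is worded accordingly.

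**Outcome ascertainment has other checks.** Table 2 also lists a clinical geneticist or pediatrician for FA21. Clefts and defects are sought from the woman's doctor or medical records, prenatal ultrasound and photographs, and an identified defect leads to a full physical examination with confirmation of cleft diagnoses. Overt cleft lip is fairly objective. This stands for the primary outcome. It protects less where judgement enters, and it does not touch adherence and follow-up effort.

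**Staff do not learn the dose.** A reader might infer that coordinators would know the arm. The documents support only a better-than-chance guess of unknown accuracy.

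**Fragility of the primary test.** A reader might infer that reclassifying three or four infants would overturn the result. Planned births give 791 × 0.05 = 39.6 and 791 × 0.025 = 19.8 events, about 40 and 20. One-sided Fisher tests with 791 per arm, against the final boundary of 0.031:

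| 0.4 mg events | 4 mg events | p |
|---|---|---|
| 40 | 20 | 0.006 |
| 36 | 20 | 0.020 |
| 40 | 24 | 0.027 |
| 40 | 25 | 0.038 |
| 34 | 20 | 0.035 |

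Four changes in one direction do not cross the boundary; it takes five added on 4 mg or six removed from 0.4 mg. Three or four would suffice only for a result already nearer the boundary, so the point does not rest on this.

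**Conclusion.** The point holds as a gap in the protection of blinding. Followed as written, the plan gives staff who assess outcomes and track compliance a marker of treatment arm, and the stated safeguard does not reach that route. The data flow is explicit in the forms tables and job descriptions, so confidence in it is high.

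How much the marker reveals rests on the trial's own hypothesis that folate separates by dose, and neither the accuracy of a guess nor the resulting bias can be computed from the document. Bias in overt cleft recurrence is probably modest. The exposure is greater for severity scoring, non-syndromic classification, other birth defects, review of losses, and adherence and follow-up effort. The change is worth making because the gap is avoidable; nothing here shows that the primary comparison is invalid.

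**What to change.** 1. Split FA16. Post-baseline serum and red-cell folate go from the laboratory to the Data Center under the subject ID, or are entered by someone with no part in follow-up or infant assessment.
2. Until unblinding, coordinators and Co-Principal Investigators receive only B12 and blood-count results. B12 safety monitoring does not need folate values and is unchanged.
3. Leave folate out of the site monitoring reports.
4. Keep the independent-physician route for a woman who asks for her results.
5. Under Blood collection, replace the sentences saying that un-blinding is impossible and that disclosure cannot affect blinding. State instead that post-baseline folate is potentially unblinding and is withheld from site research staff.

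**Cost.** A new laboratory reporting route and a revised form at four sites. This is not free: tests run at the clinics' own or local laboratories, sites currently enter all records, and the article describes no direct laboratory-to-Data-Center route.

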#### Management and retention of study subjects

All subjects will be provided with a toll-free phone number for the study that they could call at regular office hours or anytime in case of emergency for any questions they may have or issues they would like to report (pregnancy, illness, concerns, etc.).

The study will maintain periodic phone contacts with pregnant subjects to inquire on pregnancy progress and remain updated on subject’s residence. Pregnant subjects will be followed by their prenatal care provider. With subject approval, contact between the study staff and the prenatal care providers will allow follow up of the pregnancy and complications.

#### Incentives and reimbursements

Incentives, in the form of 30 Reais value food vouchers, will be provided to subjects participating in the study at enrollment and every six months thereafter to strengthen retention and motivation. All subjects will be reimbursed for transportation costs incurred to attend follow-up visits at the clinic. Postage costs for the returning of used pillboxes will be paid by the project.

As a substantial percentage of potential study subjects are economically disadvantaged, providing food vouchers is expected to help minimize the indirect burden of participation in the study, such as time lost from work or household production due to study requirements.

#### Protocol violations

A protocol violation must be reported to the Data Center within one week of its discovery. The Clinical Coordinator or the Co- Principal Investigator will complete the Protocol Violation Form. The Co-Principal Investigator will sign the form and submit it to the Data Center. Each protocol violation requires a completed form.

Possible protocol violations that require reporting to the Data Center include the following:

1. Informed consent was not obtained before randomization.

2. Subject did not meet inclusion criteria.

3. Subject did meet criteria requiring exclusion.

4. Study medication was never initiated for the patient.

5. Subject was permanently discontinued from study medication (e.g., early termination of study medication).

6. The wrong folic acid dose was given to the subject.

7. The treatment assignment of the subject was revealed to study personnel or to the subject either by request or inadvertent means.

8. Failure to take at least 50 pills in 2 months (A compliance rate of at least 80% is required).

9. Study subject withdrew consent.

10. The study subject became permanently lost to follow-up.

In situations where it is not clear whether a form is required, the Research Unit personnel should contact the Data Center staff to find out if a Protocol Violation Form is necessary.

If subjects are enrolled and later found to have been ineligible at the time of enrollment (violations 2 and 3, above), a decision to continue or terminate the study medication will be made depending on the particular inclusion/exclusion criteria violated as stated in the MOO. Except in specific situations listed in the MOO (such as when subject is permanently sterilized, has B12 deficiency and is recommended to be fully withdrawn from the study, takes epileptic drugs), subject’s enrollment will not be terminated in order to not violate the intention-to-treat principle. The medical status of a woman who discontinues the study medication will be monitored for 2 months following termination.

### Study interventions (Treatments)

#### Intervention (Treatment) descriptions

Eligible women with NSCL/P or with at least one child with NSCL/P will be randomly assigned to one of two treatment groups: one taking 4 mg and the other taking 0.4 mg of identically appearing folic acid pills. Subjects will take the folic acid preconceptionally and up to three months of gestation.

#### Delivery of interventions (Treatments)

An 8-week supply of study pills will be dispensed to subjects upon enrollment and at regular 8 week intervals to ensure uninterrupted dosing during the preconception and prenatal periods of participation. Study pills may be dispensed during in-person visits or delivered to subjects through express mail or in person visits to the clinic or subject’s home. In all sites, the pillbox provided for the previous supplementation period will be obtained from the subject to determine pill compliance.

Subjects who are confirmed to be pregnant will be advised as when to stop taking the study pills so that the intervention is limited to the first three months of gestation. If a subject experiences an adverse event, the study medication may be discontinued either temporarily or permanently after review of the principal or co-principal investigator and depending on the recommendation of the physician attending the subject when applicable.

#### Control group

The control group in this study will be the 0.4-mg folic acid group. A placebo control group is not used, as a low dose of folic acid is already recommended as a standard vitamin therapy for women during preconception and pregnancy period.

#### Related risks

Potential risks involved in this study include those of blood drawing and interview participation, which are felt to be minimal. Folic acid supplementation has overall three aspects that have already been discussed in the literature:

1. The use of folic acid may mask vitamin B12 deficiency in cases of pernicious anemia and cause irreversible neurological damage. In order to avoid this effect, a B12 assay on every subject will be performed prior to folic acid administration, and every year thereafter. Complete blood tests will be performed on collected samples at enrollment to help detect anemia. Current exposure to folic acid through fortification in the US has been reported not to increase the risk of masking anemia
[122]. This does not imply though that high doses of folic acid do not necessarily increase the masking risk, mainly for cases with B12-deficiency related neuropathy with no anemia. Yet due to the small percentage of subjects expected to have B12 deficiency, the assessment of B12 levels on a yearly basis after supplementation provides an appropriate strategy to monitor subject safety related to this issue. The added cost compared to added benefit of more frequent blood sampling to measure B12 (or other analytes) is considered high in terms of increasing the burden on subjects and lowering motivation that it should be avoided.

2. It has been suggested in the literature, though not confirmed, that high folic acid doses, such as the one used in the present study, may increase the risk of spontaneous abortions (expected spontaneous abortion rate = 15%). The numbers of spontaneous abortions will be reported and the Data Safety Monitoring Board (DSMB) will determine whether these exceed the threshold for an adverse event.

3. It has been suggested in the literature, though not confirmed, that folic acid increases twinning. Should a pregnancy result in twins, twin pregnancies in general have an increased risk of premature delivery with an intendant risk of increased mortality and morbidity for the infant, and also an increased risk of maternal complications including pre-eclampsia. Therefore, information on this matter will be collected, and the DSMB will evaluate whether the rate of twinning exceeds the threshold for an adverse event.

